| Product, Dose, Modes of Administration: | 
The intervention to be assessed is an 825-853kcal/day TDR, planned to be followed for 12 weeks, with stepped food reintroduction, using a tested energy-restricted nutritionally balanced (30% fat, <10% saturated fat) weight loss maintenance diet using food-group exchanges, plus support to increase physical activities to approach 15,000 steps/day if individually acceptable) with 30 minutes brisk-walking daily. Both intervention and control arms will continue to receive standard care under current clinical guidelines for T2DM. The intervention will be delivered by research dietitians who are trained and competent in Counterweight Plus. Process evaluation will be conducted to assess the number of patients invited, the number who engage with the programme, and completion and attrition rates. Participants will be asked to give written feedback on the programme. Assessments of quality of life, weight loss expectations, and psychological process measures will be made. Mechanistic studies will also be conducted to investigate the changes in pancreatic and liver fat. Participants will be offered the option of undergoing measurements of MR and body composition. These data will inform a larger randomised controlled trial.
 |

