## **4 Trial procedures**

Patients will all be seen at the Glasgow Clinical Research Facility for all appointments.

Patients randomised to control will be advised to continue with usual care for 3 months before coming back to receive the intervention. They will be asked not to aim to lose any weight during the initial control period, but rather to wait until they commence the intervention part of the study. An appointment will be given to the patient for 3-months' time, and they will commence the intervention at that point.

Patients randomised to intervention will commence Counterweight Plus, which includes a TDR phase followed by structured food reintroduction. This will be delivered by research Dietitians experienced in programme delivery.

**TDR phase (0 to 12-20wks):** A commercial micronutrient-replete 825-853kcal/d LELD will be provided (Cambridge Weight Plan) to replace normal foods, with ample fluids, for 12-20 weeks. Oral hypoglycaemic agents (OHA), antihypertensive and diuretic drugs will be withdrawn on commencement of TDR, and reintroduced (according to guidelines) if diabetes or hypertension returns. Aspirin will be continued in patients prescribed this because of a previous MI (prior to the previous 6 months), but will be discontinued in patients who are prescribed it purely because they have T2D. Beta-blockers will be continued in patients prescribed these for the management of angina. A soluble fibre supplement (Fybogel 2x3.5g/day) will be prescribed to avoid constipation.

Participants will return for review one week after commencement on the TDR and at 2 weekly intervals thereafter till week 12-20 (total of 7-13 appointments) and the commencement of the food reintroduction stage.

To allow some flexibility for patients whose commitments, or practical limitations vary, the TDR phase will be permitted to continue up to 20 weeks if they fail to lose >15kg by week 12. Any patient whose BMI falls below 22 kg/m^2, before week 12 will be moved forward to 'food reintroduction and weight maintenance'. Reasons for moving to food reintroduction prior to week 12 will be recorded.

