### **Appt 2-7(Weeks 0+2 – 12)**

- Measurement of weight & blood pressure
- Capillary blood glucose measured by blood glucose meter
- Psychological Process Questionnaire
- Delivery of TDR intervention as per Counterweight Plus Appointment Planner (App D)
- Waist circumference measured (if appropriate) at visit 7 (wk0+12)
- Venepuncture for HbA1c, urea and electrolytes, glucose, insulin, liver function tests, lipids.at week 12/end of TDR phase
- MR, appetite hormone and Body Composition measurements at week 12/end of TDR phase if participant has consented to these

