## **6.1 Sample size**

We aim to recruit 25 participants to the study. This figure has been chosen as this will give us enough information to assess the feasibility and acceptability of the programme to this population. We anticipate a failure to complete rate of about 25% (this may be greater at specific timepoints due to the COVID-19 pandemic). With 20 participants in a randomized comparison, the study can estimate the change in weight with a margin of error of 2.8kg assuming a standard deviation weight change over 3 months of 6kg. e.g., for an average observed weight change of 8kg (SD 6) we can estimate with 95% confidence that in the population the true weight change would lie between 5.1 and 10.7kg.

The proportion achieving remission in the combined intervention and delayed intervention groups (n=20) will be compared to the proportion achieving diabetes remission in the external DIADEM-1 trial control group (Taheri et al, Lancet Diabetes and Endocrinol, 2020) (12%; 95%CI 5%, 21%). Therefore assuming 12% remission in a usual care group (based on DIADEM), using a one sample proportion test, with 20 participants there will be 83% power to detect a significant difference if 30% of participants (n=6) or more achieve remission.

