| TOTAL DIET REPLACEMENT (APPOINTMENTS 3,4,5,6,7) |                                                                                                                                                                                                                                                                                                                                                                                                                                                                                                                                                                                                                                                                                                                                                                                                                                                                                                                                                                                                                                                                                                 |
|                                                 | 
Weight Tracker
Measure and record weight on Weight Tracker and data collection system
 
At Appointment 7
- Calculate BMI and measure waist circumference
- If >15kg weight loss is not achieved continue on Total Diet Replacement Plan up to 20 weeks
- If weight loss > 15kg NOTE: Only 1 week between Appointment 7 and 8
 
Review Getting Ready
Review weight loss expectations, and targets. Amend target if necessary
 
Total Diet Replacement Plan
Discuss progress and compliance with Total Diet Replacement Plan
Review side effects, activity, tolerance to fibre supplement and bowel habits
Ensure supply of shakes and soups - consider flavour preferences and use sachet table to calculate provision
 
Managing Difficult Times and Daily Living Diary
Review use of sections for self monitoring and relapse prevention strategies
 
Weight Tracker
Agree next appointment and record on tracker. Highlight importance of weekly self weighing
 |

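### The BMI 22 rule for ending total diet replacement lapses at week 12, yet the diet may run to week 20 on a kilogram test alone

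*Protocol*

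**What the plan says.** Three statements in the protocol govern how long a participant stays on TDR.

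- **Planned length.** The synopsis (Product, Dose, Modes of Administration) describes an 825-853 kcal/day diet "planned to be followed for 12 weeks".
- **Extension.** Section 4, TDR phase, says "the TDR phase will be permitted to continue up to 20 weeks if they fail to lose >15kg by week 12". The only test is kilograms lost.
- **Early exit.** The next sentence of section 4 says that a patient whose BMI drops under 22 kg/m² "before week 12 will be moved forward to 'food reintroduction and weight maintenance". Reasons are to be recorded only for moves made before week 12.

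The Counterweight Plus appointment planner (Appendix C) repeats the extension rule at Appointment 7, which is week 12. The practitioner is told to "Calculate BMI and measure waist circumference". The next line says that if more than "15kg weight loss is not achieved continue on Total Diet Replacement Plan up to 20 weeks". No BMI threshold or action is attached.

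Section 3.2 admits patients with BMI above 25 and below 45.

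**The concern.** The early-exit rule and the extension rule cover adjacent periods. The BMI limit applies up to week 12, and the extension that follows has no BMI limit. The protocol gives no reason for the limit to lapse just as exposure to the diet is lengthened.

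The participants affected are the leaner ones. For them the 15 kg target lies beyond BMI 22, so anyone still at or above 22 at week 12 has necessarily lost less than 15 kg and qualifies for extension. The synopsis rationale notes that South Asians are typically diagnosed at a lower BMI, so lean entrants are to be expected.

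There is also a clash at Appointment 7. In Appendix A the weighing before it is at week 10. A fall below 22 between weeks 10 and 12 is therefore first seen at week 12. Section 4 arguably requires that person to move on, while the planner says to continue.

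This is a treatment rule for participant protection. It changes no sample-size or power figure.

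**Working it through.** The protocol gives no figure of its own on this point, so the check asks whether eligible participants can fall into the gap.

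**Inputs from the protocol:** BMI limit 22, extension test 15 kg, decision at week 12, latest end of TDR at week 20 (section 4 and Appendix C); TDR starts at Appointment 1, week 0+1 (section 4.1); entry BMI above 25 (section 3.2); example weight change 8 kg, SD 6 (section 6.1).

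**Assumptions:** heights of 1.55-1.80 m; pace of loss after week 12 equal to a fraction p = 1, 0.5 or 0.25 of the earlier pace; full 8-week extension used.

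**Step 1. Who cannot lose 15 kg and stay at 22 or above?** Entry BMI below 22 + 15/h²:

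- 1.55 m: 22 + 15/2.4025 = 28.2
- 1.65 m: 22 + 15/2.7225 = 27.5
- 1.80 m: 22 + 15/3.24 = 26.6

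All three limits lie inside the eligible range.

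**Step 2. One participant: 1.65 m, entry BMI 26.** Entry weight is 26 × 2.7225 = 70.8 kg. BMI 22 is reached after losing D = 4 × 2.7225 = 10.9 kg. There are 11 weeks of TDR to week 12 and 8 more to week 20, so loss at week 20 = L12 × (1 + 8p/11), where L12 is the loss at week 12. The week-12 losses that lead to extension and a later crossing run from D/(1 + 8p/11) up to D:

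- p = 1: 10.89/1.727 = 6.3, so 6.3-10.9 kg
- p = 0.5: 10.89/1.364 = 8.0, so 8.0-10.9 kg
- p = 0.25: 10.89/1.182 = 9.2, so 9.2-10.9 kg

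With 10 kg lost at week 12, BMI is 26 − 10/2.7225 = 22.3. A further 7.3, 3.6 or 1.8 kg gives BMI 19.7, 21.0 or 21.7 at week 20. If TDR were ended on reaching 15 kg, BMI would still be 26 − 15/2.7225 = 20.5.

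**Step 3. The protocol's 8 kg example: 1.65 m, entry BMI 25.1.** Week-12 BMI is 25.1 − 8/2.7225 = 22.2, so extension is allowed. At week 20 the total loss is 13.8, 10.9 or 9.5 kg and BMI is 20.0, 21.1 or 21.6.

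**Step 4. Possible frequency, as illustration only.** Take L12 as normal with mean 8 and SD 6, and h = 1.65 m. The share below 22 by week 12 is 1 − Φ((D − 8)/6). The share extended and then crossing is Φ((D − 8)/6) − Φ((D/(1 + 8p/11) − 8)/6).

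| Entry BMI | D (kg) | Below 22 by week 12 | Extended, then crossing: p = 1 | p = 0.5 | p = 0.25 |
|---|---|---|---|---|---|
| 25.1 | 8.44 | 47.1% | 22.7% | 14.8% | 8.6% |
| 26 | 10.89 | 31.5% | 29.6% | 18.6% | 10.5% |
| 27 | 13.61 | 17.5% | 33.3% | 19.6% | 10.4% |

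**Step 5. Is there a rule elsewhere?** Section 5 and its guidance provide for two-weekly review, blood pressure and glucose triggers, and discussion of health risks with the patient and GP. Appendix E covers blood pressure. Appendix A has no TDR columns after week 12. None of these sets a BMI rule for weeks 12-20.

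**The case against.** The strongest reply is that BMI 22 is never described as a safety limit. It acts as a trigger for changing phase. Someone moved on at that point goes to 1000 kcal/day, where section 4 expects some further loss, so the protocol already accepts BMI below 22. That stands: no harm at BMI 20-22 is shown from the document. The point is the narrower one that the same BMI ends the full replacement diet before week 12 and not after it, without a reason.

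Second, section 4 only permits extension, and the planner looks like a generic programme document, since it includes orlistat advice for rescue-plan patients that this trial does not describe. A dietitian has the BMI at Appointment 7, may amend targets, and can decline to extend. This is fair for the body text. However, the planner is the working instruction cited in section 4.1, and it says to continue.

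Third, a crossing between weeks 10 and 12 is literally before week 12, so section 4 already covers it. That is a reasonable reading, but it leaves the planner in conflict with section 4.

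Fourth, the higher shares in Step 4 need an undiminished pace and the whole extension, and the 8 kg (SD 6) figure is a confidence-interval example, not a forecast for lean entrants. That also stands, and the shares are no more than illustration. At entry BMI 25.1 and 26, having crossed by week 12, where the existing rule largely applies, is the commoner outcome.

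**Conclusion.** The gap is real. As written, an eligible participant entering at a BMI of roughly 25 to 28, depending on height, can be extended on 825-853 kcal/day below the BMI that would have ended the diet a week or two earlier. In the worked cases BMI at week 20 is between 19.7 and 21.7. The textual finding does not depend on the assumptions. The sizes do: they rest on assumed heights, the pace after week 12 and full use of the extension. The frequency among the 25 participants cannot be stated, because the entry BMI mix is not given. No endpoint or power calculation is affected. It should be fixed because it is a participant-protection rule, the correction is cheap, and the study is meant to inform a larger trial that could inherit the rule.

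**What to change.** - **Section 4, TDR phase:** remove the week-12 limit from the BMI sentence, so that BMI below 22 moves a participant to food reintroduction at any TDR visit up to week 20. Record the reason at whatever week the move happens.
- **Appendix C, Appointment 7:** reword so that a participant who has not lost more than 15 kg and whose BMI is at least 22 may continue up to week 20. Using *may* matches the permission in section 4.
- **Visits:** calculate BMI from baseline height and current weight at every TDR visit, including the two-weekly extension visits, which Appendix A does not list.

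The cost is two wording edits. Height and visit weights are already collected, so in-person visits need no new measurement. Remote visits under the COVID-19 arrangements would need a stated source for weight. The downside is that a few lean participants will have a shorter TDR phase and may be less likely to reach 15 kg.

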### **Food Reintroduction (FR) phase (weeks 12-18):**

A stepped transition to food based Weight Maintenance, replacing TDR with meals which contain 30% of energy from fat. Some further modest weight loss will occur.

**Week 13:** step down to 400kcal/d LELD + 1 low-fat meal/day (c. 360-400 kcal) + 2 servings of fruit, 200mls skimmed milk and free vegetables. Total intake will be 1000kcal/day.

**Week 15:** step down to 200kcal/d LELD + 2 low-fat meals/day (c. 720-800 kcal) + 2 servings of fruit, 200mls skimmed milk and free vegetables. Total intake will be 1200kcal/day.

**Week 17:** 3 low-fat meals per day (c.1080-1200 kcal) + 2 servings of fruit, 200mls skimmed milk and free vegetables. Total intake will be 1400kcal/day.

**Week 18:** 3 low-fat meals per day (c.1080-1200 kcal) + 2 servings of fruit, 200mls skimmed milk and free vegetables. Advice to increase by 200kcal per day until weight loss maintenance achieved. Option to join BEYOND Study.

During this phase participants will attend for review appointments every 2 weeks. To allow flexibility for patients whose confidence varies, the food introduction phase will be permitted to be varied between the protocol-defined limits of 2-8 weeks before switching to full food-based weight maintenance. Reasons for moving to weight loss maintenance without completing food reintroduction will be recorded. If patients are unable to attend appointments, they will be offered telephone consultation as necessary but with encouragement to attend clinics as the preferred method of contact.

During the period of restrictions due to COVID-19

- Participants will not be seen in person for study appointments. Appointments/consultations will be carried out, by, the study research dietitian, by telephone/text/e-mail, whichever is preferred by the participant.

On completion of the feasibility study, at the end of FR we will provide participants with advice, and written information, on maintaining weight loss, which will include goal setting, self-monitoring, physical activity, relapse prevention if weight tends to rise again, and education on food labelling and eating out. Participants will then be returned to the care of their GP, who will be informed

### **Outcome Measurements – All participants**

Baseline measurements (App A), with the exception of height, will be repeated at the end of FR. All measurements will be recorded by the research dietitians.

**Height** will be measured to the nearest mm, with the Frankfort plane horizontal, using a portable stadiometer (Chasmors Ltd, London).

**Body weight** will be measured to the nearest 100g in light clothing without shoes using Class 111 approved calibrated scales. The scales will provide a printout of the participant's weight, which will be photocopied and stored securely

**MR scans** will be carried out at baseline (prior to weight loss) and repeated at the point of maximal weight loss. Participants allocated to an initial 3-month control period will have an additional MR scan carried out at the end of the control period, prior to starting the weight management intervention. Scans will be carried out at the Clinical Research Imaging Facility, Queen Elizabeth University Hospital, Glasgow. Anonymised digital data derived from the scanning procedure, will be sent by secure transfer to Advanced MR Analytics (AMRA) for analysis of fat content and distribution.

**Optional Tests:**

Measurement of Metabolic Rate (resting and during physical activity), appetite hormones and Body Composition (App B)

Participants will be asked to consider undergoing additional tests to measure Metabolic Rate, appetite hormones and Body Composition. These optional measurements will be taken at baseline, end of TDR and end of study and will be carried out in the Metabolic Laboratory, New Lister Building, Glasgow Royal Infirmary

Due to the restriction imposed by the COVID-19 pandemic it has not been possible to continue with these tests. On recommencement of recruitment these tests will not be offered to potential participants.

#### **4.1 Study schedule (App A)**

##### **Appointment (Appt) 0: Baseline (All Patients)**

- Review and discuss study participation
- Review inclusion/exclusion criteria including readiness to change screening
- Secure informed consent
- Assign study ID
- Measurement of: height, weight, waist & hip circumference & blood pressure
  - Weight measured using study scales and printout of weight countersigned by practice nurse/dietitian and CW specialist
  - Three blood pressure readings recorded 2-3 minutes apart
  - Waist and hip not measured if BMI>35kg/m^2

Venepuncture for:

- HbA1c, urea and electrolytes, glucose, insulin, liver function tests, lipids.)\*. All Fasting Sample, as per Sample Handling Manual (App C)
- Pregnancy test in women of childbearing years
- Questionnaire completion: EQ-5D, Participant Expectation and Psychological Process Questionnaire
- Randomise patient to CONTROL or INTERVENTION
- Completion of practitioner workbook by research dietitians
- Appointment made for MRI Scan

- Arrange appointment for MR, body composition and appetite hormones measurements if participant has consented to these.
- **INTERVENTION ONLY:** Samples of TDR products given to patients to allow choice of product to be used during intervention to be made.
  - **CONTROL ONLY:** Advised to continue with usual care as per current guidelines. Appointment made for 3 months for repeat
  - measurement of MR, body composition and appetite hormones,
  - MRI scan and venepuncture for HbA1c, urea and electrolytes, glucose, insulin, liver function tests,
  - commencement of weight management intervention

### **Appt 1: Week 0+1**

#### **Intervention Participants**

- Measurement of weight, blood pressure and capillary blood glucose (measured by blood glucose meter) recorded
- Oral hypoglycaemic, antihypertensive and diuretic medications discontinued
  - Aspirin only discontinued in patients who are prescribed it purely because they have T2D.
  - Beta-blockers continued in patients prescribed these for the management of angina.
- Commence TDR phase of intervention as per Counterweight Plus Appointment Planner (App C)
  - Fybogel supplement prescribed
- Appointment made for next visit

### **Appt 2-7(Weeks 0+2 – 12)**

- Measurement of weight & blood pressure
- Capillary blood glucose measured by blood glucose meter
- Psychological Process Questionnaire
- Delivery of TDR intervention as per Counterweight Plus Appointment Planner (App D)
- Waist circumference measured (if appropriate) at visit 7 (wk0+12)
- Venepuncture for HbA1c, urea and electrolytes, glucose, insulin, liver function tests, lipids.at week 12/end of TDR phase
- MR, appetite hormone and Body Composition measurements at week 12/end of TDR phase if participant has consented to these

### **Appt 8, 9, 10 (Weeks 0+13-17)**

- **Appt 8 only** ask GP to repeat HbA1c -
- Measurement of weight & blood pressure
- Capillary blood glucose measured by blood glucose meter
- Psychological Process Questionnaire
- Food reintroduction phase intervention as per Counterweight Plus Appointment Planner (App C)

#### **Appt 11 (Week 0+19, Final Appointment )**

- Venepuncture for HbA1c, urea and electrolytes, glucose, insulin, liver function tests, lipids.
- Measurement of weight & blood pressure
- Measurement of waist and hip circumference
- Psychological Process Questionnaire
- EQ-5D
- Process evaluation questionnaire
- MR, appetite hormone and Body Composition measurements if participant has consented to these

Final MR scanning will be undertaken at the point of maximal weight loss which will be either at the end of the TDR phase or end of food reintroduction

On completion of the study participants will be given advice, and written information, on maintaining weight loss, which will include goal setting, self-monitoring, physical activity, relapse prevention if weight tends to rise again, and education on food labelling and eating out. Participants will then be returned to the care of their GP, who will be informed.

#### **4.2 Study Outcome Measures**

The main study outcome measures are as follows:

- Numbers recruited into the intervention
- Programme retention
- The acceptability of the intervention to people of South Asian origin
- Weight loss achieved (kg, %), and diabetes remission. Remission is defined as a return of HbA1c to <48mmol/mol (<6.5%) that occurs spontaneously or following an intervention, and off all usual glucose-lowering pharmacotherapy for at least 3 months
- Define the mechanisms behind type 2 diabetes remission in the South Asian population

